### 2.10. Statistical analysis

A sample size calculation was performed using G*Power 3.1. A medium effect size was taken as a conservative omnibus estimation in relation to the stress assessments, based on previous studies. Large to very large effects have been observed for chronic stress [66] and basal cortisol levels [53]. Furthermore, acute stress inductions often failed to yield reliable cortisol responses, but medium to large effects have been observed for stress reactivity associations with self-reported pain responses [22].

Based on a one-way omnibus ANOVA (similar, but slightly more conservative than mixed linear models) with four groups, α of.05, desired power of.80, and a medium effect size of f = .30, 128 participants in total (n = 32 across four groups) are required. Accounting for corrupt or missing data, a sample of n = 35/group will be recruited. Additional sensitivity analyses were executed to calculate the observable effect size based on this sample in the longitudinal arm of the study (parameters: α = .05, power = .80, two groups, two measurements, correlation among repeated measures.2−.6; total sample n = 56 to account for 20% dropout/loss to follow-up). The calculation indicated that small to medium effects would be detectable (f = .17−.24) for within-between interactions in a repeated measures ANOVA.

The different outcome measures will be compared between participant groups and between different time points, using appropriate statistical tests (e.g., linear mixed model, ANOVA). Correlation analysis will be used to examine pain-stress interactions. For the longitudinal arm, analyses will focus on changes over time (i.e., baseline versus six-month follow-up), group comparisons based on pain status (i.e., recovered vs persisting) at follow-up, and interactions between changes over time in stress system functioning and the pain groups. At its core will be a linear mixed model analysis with ‘time’ as the within-subjects factor and ‘pain status group’ as the between-subjects factor. Post-hoc comparisons and adjustments for multiple comparisons will be made using Bonferroni-correction, unless more suitable post-hoc tests are identified. For all statistical tests, statistical significance will be accepted at an α of.05.

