While both acute stress and acute pain are designed to promote survival, persistence of either stress or pain is maladaptive and negatively affects well-being. Research has shown support for both elevated stress levels and dysregulation of the stress systems in people with persistent pain [12]. People suffering from chronic musculoskeletal (MSK) pain generally report higher levels of emotional distress compared to pain-free individuals [13]. Additionally, alterations in ANS functioning have been observed in chronic MSK pain conditions, as indicated by increased sympathetic and decreased parasympathetic modulation [14], blunted ANS reactivity (e.g., during a cognitive stressor) [15,16], and diminished or delayed parasympathetic reactivation during recovery from an acute stressor [15]. When stress is sustained over time, the HPA axis can become dysregulated, manifesting as either overactivity or underactivity of the system [17] . Signs of HPA axis dysregulation are observed in chronic MSK pain too, as both heightened and reduced basal cortisol levels, as well as increased and diminished cortisol reactivity [12] have been observed. These inconsistent findings might be explained not only by limited assessments of stress, but also by variations in duration and extent of the pain symptoms. Since pain is a potent stressor, individuals suffering from MSK pain may initially experience higher cortisol levels, which may lead to a rapid depletion of cortisol in response to repeated or persistent stress, potentially resulting in reduced cortisol levels as pain duration increases. This hypothesis is supported by observations in people with fibromyalgia, a widespread MSK pain condition, in which patients with a shorter disease duration showed increased hair cortisol levels, as a marker of chronic stress, while those with long disease duration show lower levels of hair cortisol (indicating a depletion of cortisol levels) [18]. This shows the importance of not only measuring hormones over a short (acute) period of time using saliva, serum, or urine samples, but to also include markers of longer (chronic) periods of cortisol exposure (e.g., cortisol concentrations from hair samples [19]). Yet, whether and how the multiple stress systems contribute to differences in pain extent and duration, and whether teasing those apart may explain some of the reported inconsistencies, remains to be tested.

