## 2. Materials and methods

### 2.1. Study design

The STRAIN study protocol was pre-registered at ClinicalTrials.gov (NCT06892977) and reported in accordance with the Strengthening the Reporting of Observational Studies in Epidemiology (STROBE) statement [23]. Recruitment for this study commenced on 8 February 2025 and is anticipated to conclude by 1 June 2026. Study completion and the release of initial results are expected by 1 December 2026. The study consists of a cross-sectional arm and a longitudinal arm (i.e., follow up at six months). A total of 140 participants will be recruited for this study, across four groups (n = 35/group): (1) a group with chronic widespread MSK pain (i.e., fibromyalgia), (2) a group with chronic localized MSK pain (i.e., non-specific low back pain (LBP) for ≥six months), (3) a group with subacute localized MSK pain (i.e., non-specific LBP for <three months), and (4) a pain-free control group (no history of chronic pain or current pain). All groups will participate in the cross-sectional arm which consists of a four-hour lab assessment at Ghent University (Ghent, Belgium) and three (consecutive) days of home assessments. Participants of the localized MSK pain groups will also participate in the longitudinal arm consisting of the same assessments, supplemented with assessing pain persistence or recovery. The study will be performed in accordance with the Code of Ethics of the World Medical Association (Declaration of Helsinki) and the international ethical and scientific quality standards accepted by the International Conference on Harmonization guidelines for Good Clinical Practice. Several patient-groups were involved in various stages of developing the study protocol, providing insights into the research and helping to minimize participant burden. The study protocol and data management plan were approved by the Medical Ethics Committee of Ghent University/Ghent University Hospital and all participants will provide written informed consent prior to study participation.

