### 2.2. Participants

Participants will be recruited through an existing database of volunteers for pain research, advertisements (e.g., social media, newsletters), and the distribution of flyers at private practices, (university) hospitals and public places.

All participants must be Dutch speaking, aged between 18 and 45 years, and have a body mass index between 18.5 kg/m^2^ and 35 kg/m^2^. Inclusion criteria for patients in the MSK pain groups are an average pain intensity of ≥2/10 on a visual analogue scale (VAS) and a pain-related disability of ≥14/70 on the Pain Disability Index (PDI) [24]. Participants of the chronic widespread MSK pain group will require proof of a primary fibromyalgia with chronic widespread pain diagnosis. As different diagnostic criteria have been used over time, researchers will check whether participants comply with the 2010 ACR-criteria [25]. To ensure that pain complaints are of MSK nature, only individuals with non-specific (primary) LBP will be included, with those suffering from LBP less than three months being eligible to participate in the subacute localized MSK pain group and those with LBP equal or more than six months being eligible to participate in the chronic localized MSK pain group. Pain-free controls should not report current pain, a history of chronic pain, or treatment for a pain condition in the last six months.

Anyone using hormonal replacement therapy, drugs ≥ 1x/week, having no stable use of medication (if applicable) one month before the study visit, a contra-indication for magnetic resonance imaging (MRI; i.e., electrical or mechanical implants, electrodes, or metal fragments in the body, being claustrophobic, weighing >150 kg), or being menopausal, pregnant, less than one year postnatal or lactating will be excluded. Furthermore, having a (history of a) psychiatric, cardiovascular, endocrine, or neurological condition (e.g., diabetes, epilepsy), spinal traumata, spinal surgery, or a severe communicative disorder or cognitive disability will not be eligible. The Dutch version of the simplified version of the Mini International Neuropsychiatric Interview (MINI) [26] based on the Diagnostic and Statistical Manual of Mental Disorders, Fifth edition (DSM-V) will be consulted in case of the presence of potential psychiatric conditions. People with LBP will be excluded if they suffer from specific LBP (i.e., LBP due to a clear identifiable pathology, e.g., lumbar radiculopathy).

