Demographical characteristics and potential confounders will be assessed, including age, biological sex assigned at birth and gendered pain dynamics, height and weight (body mass index), ethnicity, hormonal cycle and contraceptives, medication use, drugs use, alcohol use, nicotine use, educational level, occupation, comorbidities, sleep experience (quality and quantity), and used pain management strategies. These will also be used to examine whether participants complied with the instructions described below.

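### The stress-pain part of the primary aim is assigned to correlation analysis with no stated account of group; a correlation pooled over four groups selected on pain could reflect group membership alone

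*Protocol article*

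**What the plan says.** The Abstract (Aims) makes the interaction between stress and pain, at psychosocial, physiological and neural level, part of the primary aim. For that question Section 2.10 gives one sentence: "Correlation analysis will be used to examine pain-stress interactions". It mentions no group term, within-group analysis or covariate.

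For everything else the section is more open: "The different outcome measures will be compared between participant groups and between different time points, using appropriate statistical tests", with linear mixed model and ANOVA as examples. For the longitudinal arm it names a mixed model with time and pain status group, and it mentions interactions with the pain groups.

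The groups are defined by pain. Section 2.2 requires at least 2/10 on the VAS and at least 14/70 on the PDI in patients, while "Pain-free controls should not report current pain, a history of chronic pain". Section 2.11 expects the groups to have distinct stress profiles, and links these to pain sensitivity and modulation.

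Section 2.2 also states: "Demographical characteristics and potential confounders will be assessed, including age, biological sex assigned at birth", among many others. The only use spelled out is a check on compliance with instructions, introduced with the word also.

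**The concern.** When two variables both differ between groups, pooling the groups yields a correlation even if the variables are unrelated inside every group. Here pain differs by selection and stress is expected to differ. A pooled coefficient could therefore restate the group comparison and be read as evidence that people with more stress dysregulation have more pain.

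There is also a mismatch with the question. The Introduction suggests that inconsistent findings may come from differences in pain duration and extent, and cites fibromyalgia data in which "patients with a shorter disease duration showed increased hair cortisol levels", with lower levels after long disease. Whether the stress-pain relation changes with extent or duration is a question about effect modification. One correlation coefficient does not test that; a stress-by-group term does.

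**Working it through.** **The plan's own figure.** Section 2.10 states "a medium effect size of f = .30, 128 participants in total (n = 32 across four groups) are required". For a one-way ANOVA with noncentrality λ = f²N and 3 and N − 4 degrees of freedom, N = 128 gives power 0.810 and N = 124 gives 0.796. So 128 is the smallest balanced total and the plan's figure is reproduced. At N = 140 the power is 0.848. The sample size is not in dispute; f = .30 is used below as the plan's own separation of groups on a stress measure.

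**Inputs.** From the documents: four groups of 35, N = 140, two-sided α = .05, stress f = .30. Assumed, because the documents give no value: pain f = .3, .5 or .8; c, the correlation between the two sets of group means; and zero correlation within every group.

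**Formula.** With unit within-group SD, the pooled correlation created by groups alone is

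r = c · f_s · f_p / √[(1 + f_s²)(1 + f_p²)].

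The rejection rate follows from Fisher's z: δ = atanh(r) · √(140 − 3), and rate = Φ(δ − 1.96) + Φ(−δ − 1.96).

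**Worked case**, f_s = .30, f_p = .80, c = 1: r = 0.24 / √(1.09 × 1.64) = 0.24 / 1.337 = 0.180; δ = 0.1815 × 11.705 = 2.12; rate = 57%.

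| Pain f (assumed) | r, c = 1 | Rate, c = 1 | Rate, c = 0.5 |
|---|---|---|---|
| .30 | 0.083 | 16% | 8% |
| .50 | 0.129 | 33% | 12% |
| .80 | 0.180 | 57% | 18% |

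Simulation with equally spaced means (c = 1) agrees to about one percentage point: 15 to 16%, 33%, and 57 to 58%.

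**A non-monotone pattern.** Section 2.11 predicts lower basal cortisol in fibromyalgia, but higher cortisol in chronic low back pain than in controls. As an illustration, take stress means 0, 0.5, 1, −1 and pain means 0, 1, 2, 3 (controls, subacute, chronic localized, fibromyalgia). The centred cross-product is −1.25 and the sums of squares are 2.1875 and 5, so c = −1.25 / √(2.1875 × 5) = −0.38. The simulated rates are 7%, 9% and 12%, and the spurious correlation is negative. Other partly aligned or non-monotone patterns reach about 18%.

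**After adjustment for group.** With both variables centred within group (partial correlation), the simulated rate is 5%, give or take half a point, in all these settings.

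**Precision after the fix.** The correlation detectable with 80% power is tanh(2.80 / √(n − 3 − q)), where q is the number of group terms removed. One group of 35 (q = 0): tanh(2.80 / √32) = 0.46. Common within-group association over 140 (q = 3): tanh(2.80 / √134) = 0.24. Over the 105 patients (q = 2): tanh(2.80 / √100) = 0.27.

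**The case against.** The strongest reply is that the article does not say the correlations are pooled. Within-group or partial correlations are not excluded, and interaction may be used loosely for relationship. Pain is also measured before and after the stress test, and the group-by-time models of Section 2.10 can examine stress-induced change in pain directly. This stands, and it is why the error is stated as something that could happen. It does not remove the point: for this part of the primary aim the article names a method, and as worded that method neither protects against the group effect nor tests differences between groups.

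A second reply is that the highest rates need stress and pain means ordered alike, which Section 2.11 does not predict for cortisol. That also stands; hence the 7 to 18% range. Close alignment is more plausible for self-reported stress.

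A third is that some of the pooled association is of real interest, since stress may explain why groups differ in pain. But that part rests on four group means, and the group comparisons already report it.

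A reader might go further and infer that all group contrasts will be unadjusted. The documents do not support this. The tests are given as examples, mixed models accept covariates, the variables are called potential confounders, and the word also implies a use beyond the compliance check. A covariate list may sit in a fuller plan. Eligibility limits (age 18 to 45, BMI 18.5 to 35, exclusion of menopause, pregnancy, hormone replacement and unstable medication) already control part of the confounding. No size is attached to confounding by sex, because the documents give neither the sex mix per group nor a sex effect. Nor is the lack of a continuous duration term an error: the subacute and chronic groups are the planned duration contrast.

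**Conclusion.** The point holds for the correlation sentence. A method is fixed for part of the primary aim without a stated account of group, in a design where groups are selected on one variable and expected to differ on the other. If the correlations are pooled, the false-positive rate for a within-group stress-pain association is about 15 to 58% with aligned group means and about 7 to 18% with partly aligned or non-monotone means, against about 5% after adjustment for group. This rests on the plan's f = .30 for stress, assumed pain f of .3 to .8, normal data with equal variances, and no association within groups. Pooled or not, one coefficient cannot show whether the relation differs by pain extent or duration.

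**What to change.** Replace the correlation sentence with a regression, or a mixed model where measures are repeated, of the pain measure on the stress measure and group. Report the common within-group slope, and add stress × group to test whether slopes differ.

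- For experimental pain measures, use all four groups. For clinical pain intensity, use the three pain groups only: controls are selected for no pain, so their slope is essentially inestimable.
- Include a short prespecified set of confounders already collected, such as age, sex, BMI and hormonal contraception or cycle phase.
- Keep medication and pain duration for sensitivity analyses. Medication may be a consequence of pain, so routine adjustment could remove part of the effect of interest.

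No new data or participants are needed. The cost is a few degrees of freedom and low precision for group-specific slopes: at 35 per group, only a within-group correlation of about .46 is detectable with 80% power. The common slope should therefore be the main result, and the interaction should be reported with confidence intervals rather than judged by its p-value.

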To shed light on the underlying mechanisms of pain and stress interactions and their contribution to pain extent and chronification, the aim of the current STRAIN (‘stress in pain’) study is to characterize stress system functioning and its relation to pain in individuals with subacute versus chronic, and localized versus widespread MSK pain, to allow comparison of groups with different pain characteristics in terms of pain extent and duration. A comprehensive mapping of both ANS and HPA axis stress systems will be used to assess basal levels, reactivity and recovery of acute stress, and chronic stress exposure. Interactions between stress and psychosocial, (psycho)physiological, and neural correlates of pain will be investigated. Additionally, the secondary aim of this study is to characterize stress system responses over time and their role in MSK pain recovery and chronification. Therefore, stress system functioning and its interactions with pain will be reexamined after six months in the patients with subacute MSK pain.

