**Fig 1 pone.0324089.g001:**
[figure not shown]
Procedure, measures and study design. **A.** Procedure and measures. Questionnaires include the informed consent form (ICF), a demographic survey and stress and pain related constructs (i.e., questionnaires). Biochemical measures include five saliva samples during the lab assessment to measure cortisol, oxytocin and alfa-amylase and include one hair cortisol sample. Experimental pain measures include CPM (conditioned pain modulation), TSP (temporal summation of pain), HPSTh (heat pain suprathreshold) and PPTh (pressure pain threshold). Physiological stress measures include HR(V) (heart rate (variability)), BP (blood pressure), RR (respiratory rate), SC (skin conductance) and ST (skin temperature). Neural measures include structural MRI, RS-fMRI (resting-state fMRI), task-based fMRI (experimental pain – functional MRI), DWI (diffusion-weighted MRI) and pCASL (Pseudo-Continuous Arterial Spin Labeling). Before and after stress induction, using the TSST (Trier Social Stress Test), VAS (Visual Analogue Scale) and PANAS (Positive And Negative Affect Schedule) are acquired. **B.** Study design. After enrollment and the lab assessment (as displayed in A), participants collect five saliva samples at home throughout the day for three consecutive days. The chronic and subacute low back pain groups are tested again, using the same test-battery, after a follow-up period of six months.

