### 2.9. Pain recovery or persistence

The General Perceived Recovery (GPR) scale will be used to assess recovery or persistence of LBP. Patients will be dichotomized as (1) either being recovered at six-month follow-up based on pain intensity <2/10 indicated on a VAS, no pain-related disability indicated by a PDI score <14/70, and recovery indicated on a 11-point VAS whereby patients rate perceived recovery from −5 (vastly worse) to +5 (greatly improved), with zero corresponding to ‘no change’, rated on average over the past month, or (2) being non-recovered or persisting when not fulfilling these criteria, and since the duration exceeded six months, their MSK pain is considered chronic [24].

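### The core longitudinal model appears to pool subacute and chronic low back pain with no baseline-group term, so its persisting level mixes new chronification with pain that was already chronic at entry

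*Protocol article*

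**What the plan says.** **Who is followed.** Section 2.1: "Participants of the localized MSK pain groups will also participate in the longitudinal arm". The Fig 1 legend agrees: "The chronic and subacute low back pain groups are tested again, using the same test-battery, after a follow-up period of six months". So does the Abstract. The Introduction differs: stress functioning and its interactions with pain "will be reexamined after six months in the patients with subacute MSK pain".

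**How the LBP groups are defined.** Section 2.2 takes LBP of under three months as subacute, with "those with LBP equal or more than six months being eligible to participate in the chronic localized MSK pain group".

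**How outcome is classed.** Section 2.9 applies one rule to all followed patients. Those who do not meet the recovery criteria are classed as "being non-recovered or persisting when not fulfilling these criteria, and since the duration exceeded six months, their MSK pain is considered chronic".

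**How it is analysed.** Section 2.10 plans "group comparisons based on pain status (i.e., recovered vs persisting) at follow-up" and specifies a "linear mixed model analysis with ‘time’ as the within-subjects factor and ‘pain status group’ as the between-subjects factor". The core model names no subacute/chronic factor. The accompanying sensitivity calculation uses two groups, two measurements and a total of 56 after 20% dropout, and reports detectable f = .17–.24.

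**What is hypothesised.** Section 2.11 attaches the risk of chronification, defined as persistence at six months, to subacute LBP only. It also predicts that subacute and chronic LBP have different stress profiles.

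**The concern.** The secondary aim is the contribution of stress to chronification and recovery. A patient with at least six months of LBP at entry cannot become chronic during follow-up. If that patient still has pain at six months, this is continuing chronic pain, yet the status factor places it in the same level as a subacute patient whose pain has newly become chronic. The recovered-versus-persisting contrast then answers a different question from the chronification hypothesis, whatever the recovery rates turn out to be.

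A second problem is conditional. If chronic patients recover less often, the recovered level will be richer in subacute patients than the persisting level. Status then partly stands in for baseline group, and a difference between subacute and chronic LBP could be reported as a correlate of recovery.

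**Working it through.** **1. Does the plan pool the two groups?** It does not say so in those words. The two LBP groups have 35 + 35 = 70 patients, and 70 × (1 − 0.20) = 56, the total in section 2.10. Subacute patients alone would give 35 × 0.80 = 28. The stated total therefore requires both groups, and section 2.9 gives them one common outcome rule.

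**2. The plan's own detectable effect.** For the within-between interaction with two groups and m = 2 measurements, λ = f²·N·m/(1 − ρ), with 1 and N − 2 degrees of freedom. At α = .05 and 80% power:

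- N = 56 needs λ = 8.14. At ρ = .2, f = √(8.14 × 0.8/112) = .241. At ρ = .6, f = √(8.14 × 0.4/112) = .170. The stated .17–.24 is reproduced.
- N = 28 (subacute only) needs λ = 8.47. At ρ = .2, f = √(8.47 × 0.8/56) = .348. At ρ = .6, f = √(8.47 × 0.4/56) = .246.

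These figures assume an even recovered/persisting split. For a recovered share p, divide by √(4p(1 − p)). At n = 28 the range becomes .27–.38 for a 30/70 split and .31–.44 for 20/80.

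**3. Which term is exposed?** With two time points, the time-by-status interaction is a comparison of change scores. A stable baseline difference between subacute and chronic patients cancels from it. That difference biases only the status main effect. The interaction is biased only if the two groups differ in six-month change.

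**4. How large could it be?** The documents give neither recovery rates nor a group difference in change, so both are assumptions here: recovery of 50–60% (subacute) and 10–20% (chronic), 28 completers per group, no status effect within either group, and a subacute-chronic difference D in change of 0.5 or 0.8 SD. The spurious status difference is D times the gap in subacute share between the two status levels. For example, 50% and 20% give 14 + 5.6 = 19.6 recovered, of whom 14/19.6 = 71% are subacute, and 36.4 persisting, of whom 14/36.4 = 38% are subacute. The gap is 0.33, so the spurious difference is 0.5 × 0.33 = 0.165 SD.

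Simulated rejection of the unadjusted time-by-status test (20,000 runs per setting, nominal 5%):

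| Recovery, subacute / chronic | Subacute share, recovered / persisting | D = 0.5 SD | D = 0.8 SD |
|---|---|---|---|
| 50% / 20% | 71% / 38% | 8.5% | 14.0% |
| 60% / 20% | 75% / 33% | 11.4% | 20.7% |
| 50% / 10% | 83% / 36% | 12.7% | 22.2% |
| 60% / 10% | 86% / 31% | 15.7% | 30.9% |
| 40% / 40% | 50% / 50% | 5.0% | 5.0% |

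With D = 0, rejection is about 5% in every row. With baseline group in the model for change (that is, baseline group by time), it is about 5% throughout. The same arithmetic applies to the status main effect if D is read as a difference in average level, in SDs of that average.

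**The case against.** Four objections carry weight.

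- **A reader might infer that any baseline difference between subacute and chronic LBP leaks into the time-by-status interaction.** The documents do not support this. Section 2.11 describes stress profiles by group and states no difference in six-month change, and a stable difference cancels. The rejection rates above rest on an added assumption.
- **A reader might infer that the plan ignores baseline group altogether.** Section 2.10 also lists interactions between change over time and the pain groups. Section 2.11 uses that label for groups that differ in pain extent and duration, so a baseline-group-by-time analysis may already be intended. The label is not defined in section 2.10, and the core model that follows names only time and pain status.
- **A reader might infer that the follow-up of chronic patients is of no use for the secondary aim.** That goes too far. The aim covers recovery as well as chronification, and chronic patients can recover.
- **Model terms are often left to an analysis plan, which is not shown here.** This would answer a mere omission. Here the article positively names the two factors of its core model, and its detectable effect needs the combined total.

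Pooling is inferred rather than stated. If the Introduction's restriction to subacute patients governs, pooling does not arise, but the total of 56 and f = .17–.24 are then wrong.

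**Conclusion.** The point holds in two parts. The first needs no assumption about recovery rates: with both LBP groups in the arm, the persisting level combines new chronification with pain already chronic at entry, so the core contrast does not test a hypothesis stated for subacute LBP only. The documents also contradict each other on who is re-examined, and one part of the plan needs correction under either reading.

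The second part is conditional. The status main effect is confounded with baseline group if recovery rates differ between the groups; the interaction is confounded only if six-month change differs as well. The illustrative 8.5–31% rejection depends on both assumptions, and inflation vanishes when either fails. It shows what could happen and does not estimate this study's error rate.

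**What to change.** 1. Reconcile the Introduction with the Abstract, section 2.1 and the Fig 1 legend on who is re-examined, and define pain status group and pain groups in section 2.10.
2. Run the chronification contrast within the subacute group and state its detectable effect: about f = .25–.35 with 28 completers evenly split, and larger if the split is uneven.
3. In any analysis of both LBP groups, add baseline group (which protects the status main effect) and baseline group by time (which protects the interaction). This does not replace step 2, because an adjusted pooled status effect still averages over the two kinds of persistence.
4. Treat the three-way term of status, baseline group and time as exploratory at most. Under the assumed 10–20% recovery, only 28 × 0.10 = 2.8 to 28 × 0.20 = 5.6 chronic patients would recover.

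A regression of six-month pain and Pain Disability Index on baseline stress within the subacute group would be a reasonable optional addition; its absence is not part of the error.

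No new data are needed. The cost is lower precision for the chronification contrast.
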